### Active Control Group

It is an ethical imperative for long-term trials of health promotion interventions to ensure that the control group also receives essential information, which in this case would be education about childhood obesity management. To match the weekly intervention delivery frequency, the active control group will be given access to a similar secure portal where they can view weekly educational content aligned with the FHLP topics. This information is based on the FHLP curriculum and relevant information and resources from Canadian public health agencies (eg, Canada’s Guide to Healthy Living, Canada’s Food Guide, and Canada’s Physical Activity Guide). These materials are guideline based, user-friendly, and visually appealing; in addition, they include child-specific content.

At baseline, a member of the research team will meet with each control participant for a 10- to 15-minute video meeting to orient parents to the portal and ensure that they have sufficient internet literacy to access the resources. However, the control group will not receive other personal contact, such as the FHLP facilitated group sessions, physical kits, web-based cooking classes and Q&A sessions, regular check-ins, or email reminders to access the resources. All families in both study groups will maintain the same delivery schedule (10 weeks in total; Figure 1).

### Primary Outcome

Each child’s BMI *z* score will be calculated based on the World Health Organization criteria [34]. Height and weight will be self-reported at each time point via questionnaire, with parents provided with instructions to accurately measure their child’s height and weight at home [35].

### Secondary Outcomes

#### Child Physical Activity Behaviors

Changes in physical activity will be measured using accelerometry via Fitbit Inspire wrist-worn activity trackers. Seven consecutive days of daily step counts will be measured at each assessment time point. Changes in physical activity predilection and adequacy as well as perceived intrinsic motivation and competence in physical activity will be measured using the motivation and confidence subscale of the Canadian Assessment of Physical Literacy-2 [36]. Physical activity self-report will be measured using the Physical Activity Questionnaire for Older Children [37] and the Canadian Assessment of Physical Literacy-2 [36]. Changes in physical activity confidence, sedentary behavior, and family support for physical activity will be assessed using the Patient-Centered Assessment and Counseling for Exercise Plus Nutrition adolescent psychosocial measures [38]. Physical activity and screen time self-efficacy will be measured using the Family Life, Activity, Sun, Health, and Eating (FLASHE) questionnaire [39].

#### Child Dietary Behaviors

Changes in dietary behavior will be assessed using the 7-day recall questionnaire retrieved from the Behavioral Risk Factor Surveillance System survey questionnaire [40]. Healthy eating outcome expectations will be assessed using the Power Play! survey [41]. Dietary behavior self-efficacy will be assessed using the Patient-Centered Assessment and Counseling for Exercise Plus Nutrition adolescent psychosocial measures [38]. Healthy eating motivation will be assessed using the FLASHE and modified child nutrition questionnaires [39,42], and perceived cooking skills will be assessed using the Cooking with Kids questionnaire [43].

#### Child Mental Well-Being and Quality of Life

Changes in a child’s self-reported self-esteem, gratitude, and self-compassion will be measured using the self-esteem measure from Project EAT [44], the Gratitude Adjective Checklist [45], and the Self-Compassion Scale for Children [46], respectively. Children’s self-reported sleep quantity will be measured using the FLASHE questionnaire [39]. Changes in a child’s health-related quality of life will be assessed by parents (proxy report) using the Pediatric Quality of Life Inventory [47].

#### Parent Support for Healthy Family Lifestyle Environment

Parents will complete a questionnaire assessing changes in parental support, habit, role identity, and behavioral regulation in supporting their child’s physical activity and healthy eating practices using the Parent Support of Child Physical Activity and Eating Behaviors questionnaire [48], the Exercise Identity Scale [49], the Activity Support Scale for Multiple Groups [50], and the Perceived Behavioral Control Over Child Physical Activity Support Scale [51]. Changes in parental feeding practices and food preparation self-efficacy will be assessed using the FLASHE-EAT survey [52]. The structure of the home food environment and parents’ habits and dietary behaviors will be assessed using the Fruit and Vegetable At Home Survey for Parents [53]. Family eating habits and family physical activity habits will be measured using the Self-Report Habit Index [54].

#### Intervention Engagement and Attrition

For the control group, engagement with web content will be assessed based on the number of portal log-ins, the percentage of content accessed, and time spent viewing pages. For the FHLP intervention group, engagement will be assessed based on the number of Zoom-based group sessions attended as well as portal use (log-ins, the percentage of content accessed, and time spent viewing pages). Attrition will be recorded when a family withdraws from the study.

### Data Analysis

#### Overview

All analyses will be intention to treat and will include all participants with available data. Patterns of missing data in the study groups will be examined, and multiple imputations will be applied to address missing data if data are missing at random. Generalized linear mixed models will be used to compare the effectiveness of the 2 treatments in improving the primary outcome, BMI *z* score, over time. The models will include fixed effects for treatment group, time, and group×time interaction; in addition, they will adjust for baseline BMI *z* score and child’s sex. A random intercept will be included to account for within-participant correlations across repeated measures. Similar to the primary outcome analysis, generalized linear mixed models will be used to examine changes in secondary outcomes over time. Models will adjust for the baseline value of the outcome, child’s sex, and parent’s relationship to the child; in addition, a random intercept will be included to account for repeated measures.

Previous research has shown that parental involvement in child interventions can differ in ways that affect behavioral and weight-related outcomes [55]. Including this variable makes it possible to control for these potential sources of variability in the generalized linear mixed models.

In line with the sex- and gender-based analysis framework of the Canadian Institutes of Health Research [56], which encourages the thoughtful integration of sex and gender into health research, we have taken steps to reflect sex and gender considerations in our analysis plan. Specifically, we will adjust for child sex assigned at birth where biological differences may be relevant to health outcomes (eg, BMI trajectories). In the exploratory analysis, descriptive analyses will be conducted to explore whether intervention effectiveness differed between children’s gender or sex in the treatment group.

Engagement metrics will primarily be examined in subgroup and dose-response analyses. However, engagement may play a role in treatment effectiveness. Therefore, its potential inclusion as a covariate in secondary models will be explored. These exploratory analyses will help clarify the mechanisms underlying intervention impact.

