## Methods

### Trial Design

This study is a single-blind randomized controlled trial (ClinicalTrials.gov NCT06777888) with a 2×4 design (Figure 1). Participating households will be randomly assigned in a 1:1 ratio to 2 groups: FHLP intervention and control. Data will be collected at 4 assessment time points: baseline (wk 0), after the intervention (wk 10), 6-month follow-up (wk 26), and 12-month follow-up (wk 52; Figure 1). The intervention will be delivered via video chat in 3 regions across Canada (British Columbia, the prairie provinces, and Ontario), with the central site located at the University of Victoria in British Columbia.

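### The random-intercept rule assumes equal residual variance and correlation at weeks 10, 26 and 52; if variance grows by week 52, the 12-month standard error is understated, and an unstructured covariance avoids this cheaply

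*Protocol article*

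**What the plan says.** The protocol article, Methods, Data Analysis, Overview, sets the primary model: "Generalized linear mixed models will be used to compare the effectiveness of the 2 treatments in improving the primary outcome, BMI *z* score, over time". On its terms it says: "The models will include fixed effects for treatment group, time, and group×time interaction"; and "they will adjust for baseline BMI *z* score and child’s sex". The covariance rule is: "A random intercept will be included to account for within-participant correlations across repeated measures". For secondary outcomes the rule is repeated: "a random intercept will be included to account for repeated measures".

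Trial Design places the assessments at "baseline (wk 0), after the intervention (wk 10), 6-month follow-up (wk 26), and 12-month follow-up (wk 52; Figure 1", so successive gaps are 10, 16 and 26 weeks.

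The overview names no random slope, residual structure or robust standard error, and it does not exclude them. The objectives speak of a 12-month period without naming an isolated week-52 contrast. No significance level is stated.

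**The concern.** For a continuous outcome, one random intercept per child with independent residuals is compound symmetry: the same variance at every visit and the same correlation between every pair of visits. That is restrictive here for two reasons. The visits are unequally spaced. Baseline is also a covariate, so what is left unexplained at each visit depends on how well baseline predicts that visit. If baseline predicts week 10 better than week 52, which is plausible in growing children, residual variance rises over follow-up.

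The model then applies the three-visit average variance to week 52. The confidence interval for the 12-month difference becomes too narrow and a false claim of long-term benefit more likely. Long-term effectiveness is the trial's main question, so the weakness would fall where it matters most.

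**Working it through.** **Inputs from the protocol.** Follow-up visits at weeks 10, 26 and 52; 1:1 allocation; 270 enrolled; 20% expected attrition, so 270 × 0.80 = 216 children, 108 per arm. The protocol has no figure of its own on this point to reproduce.

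**Assumptions.** Correlations with baseline, SD trends, a two-sided 5% level, time as a factor, and three post-baseline outcomes.

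**Formula.** With complete data, residual variance at visit t after baseline adjustment is v(t) = SD(t)² × (1 − ρ(t)²), where ρ(t) is the correlation with baseline. The random-intercept fit uses the mean of v(10), v(26) and v(52). Hence

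- SE ratio (model/true) at week 52: r = √[mean v / v(52)]
- type I error: 2 × Φ(−1.96 × r)

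**Worked example**, ρ = 0.90/0.88/0.85, constant SD: v = 0.190, 0.2256, 0.2775; mean 0.2310; r = √(0.2310/0.2775) = 0.912; type I error 7.4%.

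| ρ at weeks 10/26/52 | SD at weeks 10/26/52 | r | Type I error |
|---|---|---|---|
| 0.88/0.88/0.88 | constant | 1.000 | 5.0% |
| 0.88/0.87/0.85 | 1/0.95/0.90 | 0.997 | 5.1% |
| 0.80/0.79/0.77 | constant | 0.967 | 5.8% |
| 0.85/0.83/0.80 | constant | 0.937 | 6.6% |
| 0.90/0.88/0.85 | constant | 0.912 | 7.4% |
| 0.93/0.90/0.85 | constant | 0.851 | 9.5% |
| 0.95/0.92/0.85 | constant | 0.797 | 11.8% |
| 0.95/0.90/0.80 | constant | 0.774 | 12.9% |

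**Simulation without dropout.** With 5,000 null trials per pattern and 108 children per arm, the last four rows gave 7.8%, 9.0%, 12.4% and 13.3% under the random intercept. A week-52 analysis of covariance on the same data gave 5.4%, 4.8%, 5.4% and 5.0%. With complete data and a baseline-by-visit term, that analysis is equivalent to the unstructured model for this contrast.

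**Simulation with dropout.** A second set used 270 children, 20% monotone dropout completely at random, a REML random-intercept fit and 5,000 runs per scenario. In the serial-decay scenarios the correlation over a gap of d weeks is c^(d/52), multiplied by 0.9 where 10% measurement error is added. Each error column is a type I error rate.

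| Assumed truth | Week-52 SE ratio | Week 52 | Week 52 minus week 10 | Average over visits |
|---|---|---|---|---|
| Equal correlation 0.8, constant SD | 1.01 | 4.4% | 4.6% | 4.8% |
| Equal correlation 0.8, SD falls to 0.9 | 1.04 | 4.2% | 4.8% | 5.3% |
| Equal correlation 0.8, SD rises to 1.1 | 0.94 | 6.2% | 5.6% | 5.4% |
| Decay c = 0.9, 10% error (ρ at week 52 = 0.81) | 0.89 | 8.2% | 7.3% | 5.5% |
| Decay c = 0.8, 10% error (ρ at week 52 = 0.72) | 0.86 | 9.1% | 8.1% | 5.5% |
| Decay c = 0.8, no error (ρ at week 52 = 0.80) | 0.75 | 14.4% | 11.7% | 6.2% |

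**Decay and falling SD together.** By the large-sample calculation with c = 0.8 and 10% error, week-52 type I error is 8.9% with constant SD, 7.9% if SD falls to 0.9 and 6.7% if it falls to 0.8.

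**The case against.** A reader might infer that the 12-month standard error is certainly too small and the 5% rate certainly lost. The protocol does not support that. Residual variance need not rise: it depends on SD(t) as well as ρ(t), and a falling SD can cancel the decay (5.1% in the second row of the first table) or make the test slightly conservative (4.2%). Parents measure height and weight at home, and the limitations section concedes error from different scales. Such error lowers all correlations and dilutes decay, which favours the 6% to 9% range. The 12% to 14% figures need a very high week-10 correlation followed by a steep fall. All of this stands.

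It is also true that neither an isolated week-52 test nor a 5% level is stated, and that the effect averaged over visits is nearly immune. That limits the point without removing it, because the group-by-time term is in the model and its week-52 versus week-10 contrast also reaches 7% to 12% under decay.

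The overview does not rule out robust standard errors or a further residual structure, and an analysis plan not shown may add them. But the article states a covariance choice for both sets of models, so a different rule elsewhere would have to be reconciled with it.

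A reader might also extend the figures to every secondary outcome. No calculation covers those outcomes, and for models with a non-identity link the equal-variance argument does not carry over to the response scale.

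**Conclusion.** The weakness is real but conditional. The stated rule is adequate if compound symmetry roughly holds after baseline adjustment. It understates uncertainty for the 12-month difference and the group-by-time contrasts if residual variance grows by week 52. Growth is plausible over gaps of 10, 16 and 26 weeks, but the document gives nothing from which to estimate it.

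The reasonable span for week-52 type I error is therefore about 5% to 14%, with the upper end reserved for steep decay. All figures rest on assumed correlations and SDs, a two-sided 5% level and time as a factor with three post-baseline visits. They concern standard errors, not the size of the estimated effect. This is an inexpensive safeguard worth adopting, not a demonstrated error in the plan.

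**What to change.** For BMI z score and continuous secondary outcomes, replace the random-intercept sentence in both places. Model the week 10, 26 and 52 values with visit as a factor, an unstructured within-child covariance and small-sample degrees of freedom such as Kenward-Roger; a baseline-by-visit term is optional. Name a fallback for non-convergence: a heterogeneous structure such as heterogeneous Toeplitz, or the random intercept with robust standard errors clustered on child. State how the degrees of freedom are handled if multiple imputation is used.

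The article reports that analysis is under way, so the change should be fixed and dated before any unblinded analysis.

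The cost is wording and code: six covariance parameters instead of two, with over 200 children. If compound symmetry is true, the loss of precision should be negligible. No power calculation was run on this, and the unstructured model itself was not simulated with dropout, so its roughly 5% error rate there rests on theory.

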#### Subgroup Analyses

Analyses will be performed to (1) describe intervention engagement and attrition to explore potential differences by parental income and education, study site, and ethnicity; (2) conduct descriptive analyses to explore whether intervention effectiveness differed between children’s gender or sex in the treatment group; and (3) evaluate the dose-response relationship in the intervention group and improvements in children’s health-related outcomes at 10 weeks, 6 months, and 12 months. Intervention dose will be defined by level of intervention engagement.

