## Discussion

### Anticipated Findings

This study aims to evaluate the effectiveness of the FHLP intervention compared to an active control group in improving BMI *z* scores and related health outcomes in children aged 8 to 12 years. On the basis of the study objectives, it is hypothesized that children in the FHLP intervention group will show greater reductions in BMI *z* scores than those in the control group over the 12-month period. In addition, improvements in secondary outcomes are anticipated, including healthier lifestyle behaviors, enhanced quality of life for children, and increased parental self-efficacy and motivation to support their child’s healthy living. The blended delivery model, which combines self-guided resources with web-based synchronous sessions, is likely to foster greater engagement and adherence, promoting sustainable behavior changes.

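### Engagement, which arises after randomisation, is considered as a model covariate and as a within-arm dose with a mechanism reading; the primary BMI z estimate is not affected

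*Protocol article*

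**What the plan says.** The Data Analysis overview lists the primary model's terms: group, time, their interaction, baseline BMI z score and child's sex, with a random intercept. Engagement is not among them, and all analyses are declared to be by intention to treat. The overview assigns engagement mainly to subgroup and dose-response analyses, then adds: "However, engagement may play a role in treatment effectiveness. Therefore, its potential inclusion as a covariate in secondary models will be explored". It closes: "These exploratory analyses will help clarify the mechanisms underlying intervention impact".

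Under Subgroup Analyses, the protocol will "evaluate the dose-response relationship in the intervention group and improvements in" child health outcomes at 10 weeks, 6 months and 12 months, with dose defined as the level of engagement.

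Under Intervention Engagement and Attrition, for controls "engagement with web content will be assessed based on the number of portal log-ins, the percentage of content accessed, and time spent viewing pages". For FHLP families, "engagement will be assessed based on the number of Zoom-based group sessions attended as well as portal use", with the same three portal measures.

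Under Anticipated Findings, the blended model "is likely to foster greater engagement and adherence, promoting sustainable behavior changes". The abstract's background likewise presents engagement as the route to better child outcomes.

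**The concern.** The reason given for adjusting is that engagement may influence how well treatment works ("However, engagement may play a role in treatment effectiveness"). In a model meant to estimate the group effect, that is a reason to leave it out. A covariate that follows allocation, and that allocation is designed to change, differs from baseline BMI z or sex. Adjusting for it does two things:

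- It removes whatever part of the effect runs through engagement.
- If an unmeasured family factor such as motivation drives both engagement and BMI z, it biases what remains, because families with equal engagement in the two arms are no longer alike on that factor.

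Comparability is a further difficulty. Zoom attendance exists only in FHLP. The portal measures exist in both arms, but the portal is the main content for controls and a supplement for FHLP.

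The within-arm dose-response has no group contrast, so it leaves the treatment effect alone. Its weakness is confounding: families who attend more may do better for other reasons. At stake is a null or adverse adjusted coefficient, or an attendance gradient, being read as evidence about how the programme works.

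**Working it through.** There is no stated figure to reproduce. The check is of the text first, then an illustration of size.

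**Text.**
1. Engagement is recorded after allocation (Intervention Engagement and Attrition).
2. The arms are built to differ on it. FHLP facilitators send weekly reminders and follow up absences (Intervention); controls receive no check-ins or reminders (Active Control Group).
3. The protocol expects the difference and expects it to carry benefit (Abstract, Anticipated Findings).
4. No method that would support a mechanism claim is described alongside the covariate or the dose-response.

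**Size. All parameters are assumptions.** Lower BMI z is better, so a positive group coefficient looks like harm. Let *s* be the arm difference in engagement in SD units. Let an unmeasured factor raise engagement with loading *a* and lower the outcome with loading *b*. Engagement has within-arm variance 1. With no effect of treatment or engagement:

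- within-arm slope of outcome on engagement = −*ab*
- engagement-adjusted group coefficient = 0 − *s*(−*ab*) = *s·a·b*
- unadjusted group coefficient = 0

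First set, where the factor explains half of engagement variance (*a* = √0.5 = 0.707):

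| *s* | *b* | *s·a·b* | Simulated (N = 2,000,000) |
|---|---|---|---|
| 0.5 | 0.1 | 0.035 | 0.036 |
| 0.5 | 0.2 | 0.071 | 0.071 |
| 1.0 | 0.1 | 0.071 | 0.072 |
| 1.0 | 0.2 | 0.141 | 0.142 |

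Second set, with *a* = *b*, 116 children per arm, 4,000 simulated trials, nominal 5% test:

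| *s* | *a* = *b* | *s·a·b* | Simulated | Group term rejected |
|---|---|---|---|---|
| 0.5 | 0.3 | 0.045 | 0.051 | 7.1% |
| 0.5 | 0.5 | 0.125 | 0.126 | 16.9% |
| 1.0 | 0.3 | 0.090 | 0.088 | 9.4% |
| 1.0 | 0.5 | 0.250 | 0.249 | 41.4% |

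With *s* = 0 there is no bias and rejection is about 5%. The unadjusted contrast averaged about zero throughout.

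**Dose-response under the same null.** The slope is −*ab*: −0.09 SD per SD of engagement with loadings of 0.3 (rejected in 16% to 17% of trials), and −0.25 with loadings of 0.5 (78%).

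**Effect wholly through engagement.** Take *s* = 1 and an effect of −0.37 per SD of engagement, so the total group effect is −0.37. Adjusted without confounding: −0.37 − 1 × (−0.37) = 0 (simulated −0.001). With loadings of 0.3 the slope becomes −0.37 − 0.09 = −0.46, and the adjusted effect −0.37 + 0.46 = +0.09 (simulated 0.090). The unadjusted contrast stayed at −0.37.

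**Comparator.** The Sample Size section gives 232 children and 80% power, but no alpha, effect size or SD. Assuming a two-sided 5% test and a simple two-group comparison, the detectable difference is (1.960 + 0.842) × √(4/232) = 0.368 SD.

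The simulations use one outcome time and ordinary least squares rather than the planned repeated-measures model.

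**The case against.** The strongest reply is that the plan is modest. The covariate is only a possibility to be explored, in secondary models, and the overview calls these analyses exploratory. It claims only that they will help with mechanisms. Much of this stands:

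- A reader might infer that the trial's treatment effect is biased. The documents do not support that: engagement is absent from the listed primary model, so the intention-to-treat BMI z estimate is untouched.
- A reader might infer that engagement is measured quite differently in each arm. That is only partly so: log-ins, percentage of content accessed and viewing time are recorded in both, and the protocol does not say which metric would enter a model.
- A reader might expect the bias to run towards apparent harm. That follows from assuming that motivation raises engagement and lowers BMI z. If families with greater difficulty attend more, the sign reverses.
- The 0.37 SD is a back-calculation, not a planned figure.
- The phrase secondary models is undefined. It could mean models of secondary outcomes, supportive models, or models within one arm. Only a model that also contains the group term gives the bias shown.

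The exploratory label does not remove the problem, because the protocol attaches a mechanism reading to the results. If secondary models means the secondary-outcome models, adjusted estimates there would also sit badly with the intention-to-treat statement.

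**Conclusion.** The concern holds for the exploratory and possibly the secondary-outcome analyses, and no further. A group effect adjusted for engagement is not the effect of being assigned to FHLP, and the within-arm dose-response is a confounded association. As written, neither can clarify mechanism. The qualitative conclusion rests on the protocol's own statements that engagement follows allocation and is expected to be raised by it, together with the ordinary possibility that family factors affect both engagement and outcome.

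The sizes (about +0.04 to +0.25 SD under a null, or loss of the whole effect when it runs entirely through engagement) are illustrations under assumed parameters. They are not estimates for this trial. Because the primary estimate is safe, this is a change that should be made, not a threat to the main result.

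**What to change.** 1. Delete the sentence proposing engagement as a covariate, so that no model estimating the group effect, for primary or secondary outcomes, includes it. This agrees with the intention-to-treat statement.
2. Report engagement descriptively by arm, with the shared portal measures separate from Zoom attendance.
3. Keep the within-arm dose-response but call it an association, adjusted for baseline predictors already collected. Such adjustment reduces confounding without removing it.
4. Remove the statement that these analyses help clarify mechanisms.

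A complier-type or mediation analysis is optional. If one is done, it should be prespecified and reported as dependent on its assumptions. A complier analysis using sessions attended, with randomised group as instrument, requires allocation to act only through sessions. The Intervention and Active Control Group sections put that in doubt, so the exclusion assumption must be stated for the kits, portal differences, cooking classes, calls and reminders.

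The cost is a change of wording. No new data are needed. As the Results section says analysis is underway, the change should be recorded and dated before engagement is related to outcomes.
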